##### Serum syphilitic serological response

In this study, clinical cure was defined as a serum RPR titer that decreased by two dilutions or showed reversion to nonreactivity within 1 year after treatment. Serum RPR titers will be measured every 3 months for 1 year after treatment.

##### Improvement of clinical manifestations

Improvements in clinical manifestations are essential in evaluating the efficacy. These improvements will be evaluated among patients with different clinical subtypes of neurosyphilis, such as meningitis syphilis, meningovascular syphilis, general paresis, tabes dorsalis, and ocular syphilis. The presence of the main clinical symptoms of each subtype (Table 2) will be assessed at baseline. Outcomes evaluated during follow-up treatment will include whether each symptom worsened, persisted (no change), recurred (initially improved, but later worsened with no further improvement), improved (clinically relevant improvement without a return to baseline), or recovered (total disappearance of symptoms).

**Table 2 Tab2:** Clinical manifestations among different subtypes of neurosyphilis

Subtype	Clinical manifestations
**Meningitis syphilis**	Fever
	Headache
	Nausea and vomiting
	Stiff neck
	Meningeal irritation
	Diminution of vision
	Diplopia
	Ptosis
	Facial paralysis
	Hearing loss
	Lower limb weakness
	Paresis, paraplegia
	Gatism
**Meningovascular syphilis**	Hemiplegia
	Aphasia
	Epileptic seizure
	Diffuse pain at the innervation site of the affected nerve
	Defecation disorder
	Hypomyotonia, amyotrophy
**General paresis**	Attention-deficit disorder
	Forgetfulness, poor judgment, and memory
	Cognitive disorder
	Dementia
	Depression
	Personality changes
	Delusion
	Mania
	Amentia
	Epileptic seizure
	Stroke
	Dysarthria
	Hypotonia in the face and limbs
	Involuntary movements of the face, tongue, and hands
**Tabes dorsalis**	Sensory ataxia
	Lightning pain in the lower limbs
	Uroschesis
	Visceral crises
	Lower extremity muscle tone is low
	Charcot joint
	Optic atrophy
	Argyll Robertson pupil
	Tendon reflexes decreased or absent
**Ocular syphilis**	Blepharoptosis
	Limitation of eye movement
	Diplopia
	Diminution of vision
	Blind
	Bulbar conjunctival hyperemia
	Visual field defect
	Metamorphopsia
	Color vision
	Dimmed vision
	Aethomma, floaters

#### Secondary outcomes

##### MMSE score

General paresis is the most frequently reported clinical presentation of neurosyphilis in China [17], with patients having different levels of cognitive impairment. The Mini-Mental State Examination (MMSE), one of the earliest and most widely used brief cognitive assessment tools [18], is utilized to evaluate the severity of dementia among patients with general paresis [19]. In this study, MMSE scores will be determined before treatment and at each follow-up to determine the degree of recovery from cognitive impairment among patients presenting with general paresis at baseline.

##### CSF protein concentrations

Protein concentration in the CSF is a diagnostic indicator of neurosyphilis and will be examined at 6-month intervals. This parameter was defined as a secondary outcome because of its insufficient sensitivity and specificity for the assessment of disease severity [4, 20]. A significant decrease or return to the normal range of CSF protein concentrations (≤ 500 mg/L) will be defined as indicative of effective treatment.

##### Imageological findings

Magnetic resonance imaging (MRI), computed tomography (CT) of the brain, and electroencephalography (EEG) are commonly used as auxiliary examinations for patients with neurosyphilis, with abnormal neuroimaging findings frequently due to CNS inflammation and impairment. Neuroimaging may also show progression in patients who have no neurological symptoms or signs and in patients who receive standardized treatment [21]. In this study, results of patients who undergo imaging examinations before and after treatment will be evaluated. Outcomes will be categorized as no response (no change after treatment), improvement (improved without a return to baseline), and recovery (return to normal).

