### Outcomes

All parameters will be assessed at baseline before treatment (T0) and at follow-up timepoints 3 (T1), 6 (T2), 9 (T3), and 12 (T4) months later.

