### Blinding

Because of the obvious differences between modes of administration of ACPG and ceftriaxone, both patients and clinicians will be aware of their group assignment, precluding the possibility of a double-blind study design. However, the outcome assessors and data analysts can be masked (blinded) to the treatment assignment. This prospective randomized open-blinded endpoint (PROBE) study design is frequently used to improve the reliability of analytic results [26].

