### Statistical analysis

All statistical analyses will be performed using SPSS 21.0 statistical software by biostatisticians blinded to group assignment. Missing data for the primary outcome will be imputed using the multiple imputation method. Serum and CSF RPR titers will be analyzed after log_2_ conversion. Normally distributed continuous variables in the two groups will be compared by *t* tests, and categorical variables will be compared by the *χ*^2^ test or *Fisher’s *exact test, as appropriate. Nonparametric variables will be compared by rank sum tests. The correlation between serum and CSF RPR titers will be analyzed using Spearman’s rank correlation tests. Based on the assumption that there are no obvious correlations between primary outcomes and that it will be impossible to determine which outcome has greater weight, the weights of these primary outcomes will be evaluated using the “Experts Scores” algorithm, with “overall response” to treatment evaluated according to the total efficacy scores from these primary outcomes. The results of each primary outcome will also be evaluated separately. The non-inferiority margin will be set at 10 percentage points for the absolute difference between the two groups. If the standard for non-inferiority is reached, all primary and secondary outcomes will be tested for superiority (*P*<0.05). Non-inferiority will be considered reached if conclusions drawn from the intention-to-treat (ITT) population, consisting of all patients who met the inclusion criteria, were randomized, and started treatment, and the per-protocol population, consisting of all patients with good compliance and who followed the protocol to completion of the treatment regimen, are consistent. Univariate analyses will be performed to identify potential factors associated with the treatment outcome, with variables having a *P* value ≤0.10 in univariate analyses included in a multivariate logistic regression model. Odds ratios (ORs), adjusted ORs (aORs), and their 95% confidence intervals (CIs) will be calculated. A two-sided *P value* <0.05 will be considered statistically significant. Because the efficacy and safety of ceftriaxone and ACPG are clear and both are recommended by Chinese National Guidelines, this trial will not include interim analyses.

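### Imaging is compared only in patients scanned both before and after treatment, a set fixed after randomisation, yet it falls under the superiority tests that follow non-inferiority

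*Protocol article*

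**What the plan says.** Imaging is a secondary outcome of the protocol article. The section Imageological findings says that MRI, CT and EEG "are commonly used as auxiliary examinations for patients with neurosyphilis". It then sets the analysed population: "results of patients who undergo imaging examinations before and after treatment will be evaluated". The scale has three levels: "Outcomes will be categorized as no response (no change after treatment), improvement (improved without a return to baseline), and recovery (return to normal". The section names no required modality or visit.

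The section Blinding says that "both patients and clinicians will be aware of their group assignment", while "the outcome assessors and data analysts can be masked (blinded) to the treatment assignment".

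The section Statistical analysis says that, if the non-inferiority standard is met, "all primary and secondary outcomes will be tested for superiority" at P<0.05. Imaging is not exempted. Categorical outcomes are compared by chi-square or Fisher's exact test.

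**The concern.** Randomisation makes the arms comparable as randomised. It does not keep them comparable once patients are selected by something that happens later. A repeat scan is such an event, and a patient without one has no imaging score. In an open-label trial, knowledge of the arm can affect who is re-scanned, whether through the clinician's request or the patient's willingness to return.

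If the link between response and re-scanning differs by arm, equally effective drugs can show different imaging response rates, and a real difference can equally be hidden. The result could still be published with a superiority P value and read as randomised evidence. That matters in a trial meant to inform treatment guidelines.

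The neighbouring MMSE outcome shows that the plan can do this differently. It is also restricted to a subset, but to patients with general paresis at baseline, scored at each follow-up. That subset is fixed before treatment and keeps the randomised comparison; the imaging subset does not.

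**Working it through.** **Sample size in the plan.** No figure is given for imaging. The overall calculation reproduces: (1+1.5)²/(1−1.5)² × 7.85 = 25 × 7.85 = 196.25 events; 196/0.85 = 230.6 patients; 230/0.80 = 287.5, which the plan rounds to 5 × 58 = 290. At 1:1 this is 145 per arm.

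**Assumed inputs (none is in the document).** True imaging response (improvement or recovery) is t = 60% in both arms, so the drugs are equal. Every patient has a baseline scan that could be scored for change. In arm A, 60% are re-scanned regardless of response. In arm B, the chance of a repeat scan is r₁ for responders and r₀ for non-responders.

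**Formulas.** Share re-scanned = t·r₁ + (1−t)·r₀. Response rate seen among those re-scanned = t·r₁ / [t·r₁ + (1−t)·r₀].

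- Arm A, 0.60/0.60: 0.36/0.60 = 60.0%, with 60% re-scanned (87 of 145).
- Arm B, 0.50/0.70: 0.30/(0.30+0.28) = 0.30/0.58 = 51.7%, with 58% re-scanned (about 84). The false gap is 8.3 points.
- Arm B, 0.50/0.80: 0.30/(0.30+0.32) = 0.30/0.62 = 48.4%, with 62% re-scanned (about 90). The false gap is 11.6 points.

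**False-positive rate** (pooled two-proportion z-test, two-sided 5%):

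| Arm B re-scan chances (responders / non-responders) | False gap | Standard error | Gap / standard error | Chance of P<0.05 |
|---|---|---|---|---|
| 60% / 60% | 0 | 0.074 | 0 | 5% |
| 50% / 70% | 8.3 points | 0.076 | 1.09 | about 19% |
| 50% / 80% | 11.6 points | 0.075 | 1.55 | about 34% |

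**Sensitivity.** A second set of assumed rates has half of arm A re-scanned regardless of response. Arm B chances of 45%/55% then give a 4.9-point gap and about 9%; 40%/60% give 10.0 points and about 22%; 30%/70% give 20.9 points and about 70%. With a true response of 40% or 80% in place of 60%, these three rates become about 8–9%, 17–22% and 56–66%. If only 80% of each arm remains in follow-up (0.80 × 145 = 116), the two main scenarios give about 16% and 28%.

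**When there is no bias.** If the link between response and re-scanning is the same in both arms, equal drugs show equal rates, even though both rates are distorted. Under equal efficacy, the false gap needs selection that differs by arm.

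**The case against.** **Who orders scans.** A reader might infer that clinicians who know the arm decide who is re-imaged. The text does not say so. Describing imaging as auxiliary and commonly used concerns general practice, and the blinding section says only that clinicians know the allocation. This stands, and the point does not depend on it: a post-randomisation entry condition in an open-label trial is enough.

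**The schedule figure.** Fig. 2 is not shown and may list imaging visits. The restriction might then mean only that a change category needs two scans, and the problem would be ordinary missing data rather than chosen scanning. That would lessen the concern, but the evaluation would still be limited to patients scanned twice.

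**A contradiction with the Outcomes lead-in.** A reader might also see a conflict with the statement "All parameters will be assessed at baseline before treatment (T0) and at follow-up timepoints" 3, 6, 9 and 12 months. That sentence is generic, and other sections narrow it too: CSF RPR at 6 and 12 months, CSF protein at 6-month intervals, MMSE in general paresis only. A cross-reference would help, but this is not a material contradiction.

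**Missing secondary data.** The article names multiple imputation only for the primary outcome. Handling of missing secondary data is commonly left to the analysis plan, so that silence is not held against the protocol.

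**Is the bias likely?** The document gives no evidence that re-scanning differs by arm. It describes both drugs as guideline-recommended with clear efficacy and safety. At the assumed rates the expected gaps would not themselves be significant (P about 0.28 and 0.12). Both observations are fair. The harm is a raised chance of a false finding, not a certain one.

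**Conclusion.** The point holds as a defect in how one secondary outcome is to be analysed. The stated rules define the imaging set by a post-randomisation event, leave selection into it open to knowledge of the arm, and then include imaging in conditional superiority testing without a caveat.

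The size cannot be taken from the document. Under the assumptions shown, the false gap is about 8 to 12 points and the false-positive rate about 19% to 34% with 145 per arm. It is zero and 5% if re-scanning is unrelated to response, or related to it in the same way in both arms.

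A reader might conclude that the trial's main result is compromised. It is not: imaging is not a primary outcome, and superiority testing begins only after non-inferiority has been reached. The change is worth making because it is cheap, not because the main conclusion is at risk.

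**What to change.** In Statistical analysis, exempt imaging from the superiority tests. In Imageological findings, state that imaging is reported descriptively, giving by arm the number with baseline imaging, the number re-imaged, and the reason for the repeat scan (scheduled or clinically triggered). Say there how this relates to the general assessment schedule.

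If a between-arm comparison is kept, define its population at baseline as all randomised patients with abnormal baseline imaging, label it exploratory, and show how the result changes under different assumptions about patients not re-imaged. Best-case/worst-case bounds should not be the main tool. With 40% not re-scanned in each arm, the difference between arms could move by 40 points in either direction, a span of 80 points, which says little.

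The cost is wording plus recording the reason for each repeat scan. No extra scans are needed. One secondary P value is given up or becomes exploratory.

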##### Adverse events

The JHR is the most common transient clinical phenomenon that occurs in patients infected by syphilis who undergo antibiotic treatment. JHR can manifest as fever, chills, rigor, nausea and vomiting, headache, tachycardia, hypotension, hyperventilation, flushing, myalgia, and exacerbation of skin lesions. Although occurring very rarely in patients with late syphilis, the JHR can occur in 75% of patients with general paresis [22]. The present study will compare JHR rates in the ACPG and ceftriaxone groups. Other adverse events due to treatment, such as neurotoxicity and neutropenia, will also be analyzed [23]. All adverse events after treatment and at each follow-up visit will be recorded.

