### Management of data and biological samples

Each research center should assign investigators to collect clinical information from patients, including demographic characteristics (patient name, ID number, telephone number, and other identifying information, which will be kept anonymously), history of sexually transmitted disease (STD) infection and treatment, lifestyle, information acquired at each visit (including clinical manifestations, results of laboratory tests and auxiliary examinations, and diagnosis and treatment information), and the occurrence and management of adverse events. All adverse event data will be systematically collected using standardized coding MedDRA, with the details recorded in a case report form (CRF). At each research center, several researchers will be assigned to call the enrolled patients to remind them of each follow-up visit. Real-time telephone consultations and psychological counseling can be provided after treatment to improve follow-up compliance. All data on each patient will be double entered into an electronic CRF (eCRF). Data from patients who did not complete follow-up and voluntarily withdrew from the study will be retained with other data.

At the end of the trial, the investigators at each branch center will submit the eCRFs of all patients to the head research center. Information on the eCRF for each patient should be complete and signed. All data will be submitted to the Data Monitoring Committee (DMC) of the head research center and uploaded to the Resman Clinical Trial Management Public Platform (http://www.medresman.org.cn/pub/cn/proj/search.aspx) within 6 months after completion of the trial. The results of the trial will be published in a peer-reviewed journal. Documents of all participants will be preserved for at least 10 years after publication, allowing the original data to be accessed if necessary. The clinical data will be used in future studies with the consent of the participants.

The specimens (blood and CSF) used in this trial will be collected by hospital laboratory staff for diagnosis and assessment of the clinical efficacy of treatments for neurosyphilis. After analysis, the samples will be destroyed and will not be kept for future studies.

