This trial will meet high methodological standards, such as strict inclusion and exclusion criteria, adequate randomization and concealment of allocation, a PROBE design, the inclusion of independent statisticians, and multilevel quality control. These factors increase the credibility of the clinical trial results. Second, comprehensive outcomes will be evaluated to compare the efficacy of ACPG and ceftriaxone. Previous clinical trials have evaluated the efficacy of treatment for neurosyphilis based on rates of serological cure, clinical cure, and normalization of CSF-WBC counts and on protein concentrations [17, 27–30]. Several studies have also evaluated the use of neuroimaging examinations to determine the efficacy of neurosyphilis treatments [21, 31]. The present trial will also evaluate clinical improvements (including MMSE scores), adverse events, time to recovery, and recurrence of neurosyphilis. Evaluation of improvements in clinical manifestations will include improvements of the most common clinical manifestations of each clinical subtype of neurosyphilis during follow-up. These parameters have not yet been evaluated in previous studies and may provide strong evidence to determine the efficacy of treatment. Adverse events will be assessed to determine the safety of ceftriaxone. Disease recurrence, time to recovery, and 1-year follow-up results in patients with neurosyphilis may provide evidence for evaluating the long-term efficacy of the two drugs. In addition, because neurosyphilis patients are frequently lost to follow-up, the sample size calculated using a standardized formula has been increased to improve the reliability of outcomes. Finally, analysis of clinical factors, such as smoking, alcoholism, stage of disease (early or late neurosyphilis), asymptomatic or symptomatic status, baseline serum and CSF RPR titer [32], and CSF-WBC counts and protein concentration, may enable the identification of the factors related to treatment efficacy and obtain evidence for providing a more personalized and accurate treatment regimen.

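### All adverse events are recorded, but beyond JHR the plan names for analysis those attributed to treatment, with no statement that attribution is masked in an open-label trial

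*Protocol article*

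**What the plan says.** Three statements in the protocol article, Adverse events (under Secondary outcomes), define what is collected and what is analysed:

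- JHR gets a direct comparison: "The present study will compare JHR rates in the ACPG and ceftriaxone groups".
- Other harms enter the analysis through a causal qualifier: "Other adverse events due to treatment, such as neurotoxicity and neutropenia, will also be analyzed".
- Recording has no such qualifier: "All adverse events after treatment and at each follow-up visit will be recorded".

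Management of data and biological samples confirms that collection is complete and coded: "All adverse event data will be systematically collected using standardized coding MedDRA". It gives the collecting to investigators at the centres: "Each research center should assign investigators to collect clinical information from patients". It does not say who decides whether an event was caused by treatment.

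Blinding states that "both patients and clinicians will be aware of their group assignment, precluding the possibility of a double-blind study design". It adds that outcome assessors and data analysts can be masked, without mentioning adverse event attribution.

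Statistical analysis does not mention adverse events. The Discussion gives the purpose: "Adverse events will be assessed to determine the safety of ceftriaxone".

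**The concern.** Randomisation protects a comparison of all events that occur after allocation. It does not protect a comparison of events selected afterwards by a judgement that may itself depend on allocation. A causal filter is such a selection, and here the people at the bedside know the arm.

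The filter is harder to apply in this disease than in most. Of the two harms named, neurotoxicity overlaps with Table 2, which lists epileptic seizure, delusion, mania and cognitive disorder as features of neurosyphilis. A seizure in a patient with general paresis can be read as drug or disease, and knowing which drug was given can tip the reading.

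The safety conclusion on ceftriaxone is at stake. Differential attribution can create a difference that does not exist or hide one that does, and events put down to the disease leave the safety comparison.

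**Working it through.** **Step 1: the text.** The recorded set is all adverse events. The set named for analysis, beyond JHR, is those attributed to treatment. The two differ by a causality judgement. No section commits to an all-cause comparison, and none says that this judgement is masked.

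**Step 2: inputs.** The article gives no adverse event rate and no attribution rate, so there is no planned figure to reproduce. Only the arm size comes from the document: 290 randomised 1:1, so 290 / 2 = 145 per arm. All rates below are assumptions.

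**Step 3: formulas.** Analysed rate = true rate × probability that an event is attributed to treatment. For analysed rates p1 and p2, with n = 145 per arm, d = |p1 − p2| and p̄ = (p1 + p2)/2, the chance that a two-sided 5% test is significant is approximately

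Φ[(d − 1.96 × SE0) / SE1], where SE0 = √(2p̄(1 − p̄)/n) and SE1 = √((p1(1 − p1) + p2(1 − p2))/n).

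**Step 4: no true difference.** The first arm has 60% attribution throughout.

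| True rate, both arms | Attribution, other arm | Analysed rates | False difference | Chance of P<0.05 |
|---|---|---|---|---|
| 20% | 60% | 12% vs 12% | 0 points | 5% (nominal) |
| 20% | 50% | 12% vs 10% | 2 points | about 8% |
| 20% | 40% | 12% vs 8% | 4 points | about 20% |
| 20% | 30% | 12% vs 6% | 6 points | about 43% |
| 40% | 50% | 24% vs 20% | 4 points | about 13% |
| 40% | 40% | 24% vs 16% | 8 points | about 40% |
| 40% | 30% | 24% vs 12% | 12 points | about 76% |

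Worked example, 12% vs 8%: p̄ = 0.10, SE0 = √(2 × 0.10 × 0.90/145) = 0.0352, SE1 = √((0.1056 + 0.0736)/145) = 0.0352, so (0.04 − 1.96 × 0.0352)/0.0352 ≈ −0.83 and Φ(−0.83) ≈ 0.20.

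If the true rates are equal and every recorded event is counted, the expected difference is zero in every row.

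**Step 5: a true difference hidden.** Take true rates of 20% vs 10%. Counting all events, the chance of P<0.05 is about 67%. With attribution of 50% in the first arm and 90% in the second, the analysed rates are 0.20 × 0.50 = 10% and 0.10 × 0.90 = 9%, and the chance falls to about 6% (both tails counted).

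**The case against.** The strongest reply is that two stronger statements a reader might infer are not in the text.

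- *That unmasked clinicians judge causality.* The article names no judge. Centre investigators are assigned to collect adverse events, not to attribute them. Adverse events sit among the secondary outcomes, and outcome assessors can be masked, so masked attribution is not excluded. This stands. The supportable statement is that the judgement may be made with knowledge of the arm and that nothing says otherwise.
- *That treatment-attributed events are the sole events to be analysed.* The sentence could be a loose list of harms of interest, and the Discussion speaks of assessing adverse events without qualification. The restriction is the natural reading beside the unqualified recording statement, but it is an inference.

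Further points on the other side:

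- A journal article may leave the causality procedure and table layout to the full protocol or analysis plan. Their absence is therefore no finding. The point rests on the qualifier that the article does state.
- JHR features also overlap with the meningitis symptoms in Table 2, but this does not help the argument because JHR is compared separately. Neutropenia, the other named harm, is a laboratory finding and not a Table 2 feature. The overlap argument applies to neurotoxicity.
- Events called disease do not all disappear. Worsening or recurring symptoms feed the clinical, nonresponse and recurrence outcomes, and withdrawal is counted for any reason. These are not safety comparisons, so they reduce the loss without removing it.
- Nothing in the article suggests that attribution will differ by arm. It calls the efficacy and safety of both drugs clear. The illustration shows what would follow if attribution differed, not that it will.

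**Conclusion.** The point holds in a limited form. The article names a causality-filtered analysis for adverse events beyond JHR, records all events, and makes no commitment to an all-cause comparison. In an open-label trial with no statement that attribution is masked, the filter can bias a comparison on which a safety conclusion is meant to rest.

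The size is unknown. On the assumed inputs, the chance of a false significant difference runs from about 8% to 43% at a 20% event rate and from about 13% to 76% at 40%. It stays at the nominal 5% if attribution is equal. These figures rest wholly on assumed event and attribution rates and on all 145 patients per arm contributing.

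This is an inexpensive improvement, not a serious flaw. No data are lost, the all-cause analysis remains possible, and the non-inferiority conclusion on efficacy is untouched.

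**What to change.** In Adverse events, replace the sentence on events attributed to treatment with a comparison by arm of all recorded, MedDRA-coded adverse events, serious events and events leading to discontinuation, regardless of attributed cause. Keep the JHR comparison as it is. Show treatment-attributed events as a supplementary table, and state who judges causality and whether that person is masked.

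The cost is a change of wording and one extra table, because the events are already recorded and coded. The tables will carry more background events, which makes them less specific to drug effects; the supplementary table answers that. The change removes the attribution step from the main comparison. It does not remove any difference in how readily events are reported in an open-label trial.
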